### Power and sample size

A convenience sample of 180 carers of older adults with Alzheimer’s disease/related dementias and MCC will be recruited to participate in this study; 90 in Ontario, and 90 in Alberta. This sample size (45 per group × 2 groups × 2 provinces) will provide 80% power (alpha = 0.05) to detect a mean difference of 2 increases in the MCS of the SF12v2 (primary outcome) with a standard deviation of 2.5.

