### Primary outcome measures

The primary outcome variable is the **Mental Component Summary (MCS) score** from the short form Health Survey (SF12.v2) [19]. This outcome was selected because the intervention was designed to primarily address the psychosocial impacts associated with transitions experienced by carers of persons with ADRD [20]. The secondary outcome variable is the Physical Component Summary (PCS) score.

The **SF12.v2** consists of 12 questions that measure functional health and well-being from the client’s perspective, and it has been used in a number of studies involving community-dwelling older adults. The SF12.v2provides scores for eight health domains (physical functioning, role-physical, bodily pain, general health, vitality, social functioning, roles, and emotional and mental health), and two summary, psychometrically-based scores: a physical component summary (PCS) and mental component summary (MCS). The PCS and MCS have a maximum score of 100.The SF-12.v2 has good internal consistency reliability, construct validity, and distinguishes between groups of patients with known clinical differences in physical and mental health, in a variety of client populations [21, 22].

We hypothesize that hope and general self- efficacy (confidence in the ability to deal with difficult situations) will be the mechanisms through which HRQoL will change over time (see Fig. 2). Hope will be measured by the **Herth Hope Index**, which is a 12-item, 4-point Likert scale that assesses three dimensions of hope: temporality and future, positive readiness and expectancy, and interconnectedness [23]. Scores range from 12 to 48, with higher scores indicating greater hope. The HHI has been found to be reliable and valid measures with family carers [24, 25]. The **General Self-Efficacy Scale** [26] will be used to measure carers’ level of self-efficacy. The GSES is a 10-item scale that is designed to assess one’s ability to deal with adverse situations. Total scores range from 10 to 40, with higher scores indicating greater self-efficacy. The GSES has been reported to be reliable and valid measure across a number of populations [27].

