#### Question 1: primary outcome analysis

Intent to treat analysis using generalized estimating equations (GEE) was selected as the analytical model. Analyses will be implemented using PROC GENMOD in SAS Version 9.3 [31]. The GEE model will include the following variables: group (intervention, control), time, group x time interaction, and selected covariates (if a significant intervention effect is detected in a model without covariates). If included in the GEE, covariates will include age, gender and other variables where significant group differences are seen in a comparison at baseline. The outcome of interest is a continuous variable SF12v2 MCS. The variable of primary interest is the group and time interaction, which indicates a treatment effect if statistically significant [32]. Time will be modelled based on assessment of a plot of the mean MCS values for both groups at each time period, with time treated continuously if a linear trend is observed and categorically if a non-linear trend is observed.

GEE does not require a normal distribution and SAS offers a number of distributional choices and associated link functions. The distribution (and link) selected will be the one that best matches the distribution of MCS scores for study participants. MCS is negatively skewed in many populations, with few suitable functional distributions for this pattern. If the distribution of MCS scores is significantly negatively skewed, a reflected transformation will be applied to the MCS scores in an effort to normalize them [33] and then the normal distribution and identity link will be applied to the transformed data in the GEE.

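### The stated 80% power does not follow from the stated inputs: 90 carers per arm, a difference of 2 and an SD of 2.5 give 99.96%.

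*Protocol article*

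**What the plan says.** The protocol article's section 'Power and sample size' holds the only power statement in the document.

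- Sample size: "A convenience sample of 180 carers of older adults" with ADRD and MCC, laid out as "45 per group × 2 groups × 2 provinces". That is 90 per arm, in line with the 1:1 allocation under 'Recruitment and randomization'.
- Claim: this number "will provide 80% power (alpha = 0.05) to detect a mean difference of 2 increases in the MCS of the SF12v2 (primary outcome").
- Spread assumed for that claim, at the end of the same sentence: "with a standard deviation of 2.5".
- Not said in that section: whether alpha is one- or two-sided, and whether 2.5 is the SD of a score, of a change or of a baseline-adjusted score. No correlation, design effect, multiplicity correction or loss allowance is given that would link the inputs to the result.

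Under 'Question 1: primary outcome analysis' the MCS is analysed by GEE: "The variable of primary interest is the group and time interaction, which indicates a treatment effect if statistically significant".

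**The concern.** A sample size, a difference, an SD and an alpha together determine the power of a two-group comparison. Here all four are given and the result beside them does not match. This is therefore an inconsistency inside one sentence, not a detail that a condensed article has left to a fuller document. A fuller document could explain where the sentence came from, but could not make it true as written.

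What is at stake is whether the trial is sized sensibly for its primary outcome. If the SD of 2.5 is right, the trial is about 3.5 times as large as its own target requires (90/26 = 3.46). If the SD is the wrong entry, the real power for 2 points could be well below 80%. A reader of the article cannot tell which of these situations applies.

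**Working it through.** **Inputs**, all from 'Power and sample size': n = 45 × 2 = 90 per arm; difference δ = 2; SD σ = 2.5; α = 0.05, taken as two-sided because the text does not say.

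**1. The plan's own figure.** Standard error of the difference: σ√(2/n) = 2.5 × √(2/90) = 0.373. Noncentrality: 2 / 0.373 = 5.37.
- Normal approximation: Φ(5.37 − 1.96) = 99.97%.
- Noncentral t, 178 degrees of freedom: **99.96%**.
- One-sided alpha raises it further, to 99.99%.

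The stated 80% is not reproduced.

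**2. Size needed for 80%.** Normal formula: n = 2σ²(1.960 + 0.842)²/δ² = 2 × 6.25 × 7.85 / 4 = 24.5, so 25 per arm. By the t-test, 25 per arm gives 79.1% and 26 gives 80.7%, so **26 per arm**, 52 in total.

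**3. Other readings of the sentence** (noncentral t, two-sided, unless marked).

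| Reading | Power |
|---|---|
| One province only, 45 per arm | 96.4% |
| Difference in changes, SD 2.5 at each visit, correlation 0 (SD of change 2.5√2 = 3.54), 90 per arm | 96.5% |
| The same, 45 per arm | 75.6% |
| Group-by-province interaction, SE 2.5√(4/45) (normal approximation) | 76.5% |
| Bonferroni alpha/8, 90 per arm (normal approximation) | 99.6% |

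Any positive within-person correlation raises the change-score rows. For the pooled comparison to fall to 80%, loss would have to be about 71% (1 − 26/90), or a design effect near 3.6 would be needed (90/3.6 = 25 per arm; 80.7% by the normal approximation). The article states neither, and carers are randomised individually.

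**4. Working backwards from 90 per arm and 80%.** The t-test detects a standardised difference of 0.420.
- At SD 2.5 the detectable difference is 0.420 × 2.5 = 1.05 points.
- For a difference of 2 the SD may be at most 2 / 0.420 = 4.76.

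**5. If the SD is the misstated input.** SDs of 5, 8 and 10 are assumptions; the article gives none of them.

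| SD | Power for 2 points, 90 per arm | Difference detectable with 80% power |
|---|---|---|
| 2.5 (stated) | 99.96% | 1.05 |
| 5 (assumed) | 76% | 2.1 |
| 8 (assumed) | 39% | 3.4 |
| 10 (assumed) | 27% | 4.2 |

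**The case against.** **Some reading might give 80%.** One does. Take the target as a difference in changes, use one province (45 per arm), and assume a within-person correlation of 0.10. The SD of the change is then 2.5 × √(2 × 0.9) = 3.35 and power is 79.9%. So it would be too strong to infer that no reading reaches 80%. But this one needs a correlation that the article does not state, and it describes half the trial when the sentence credits the power to all 180 carers. It does not rescue the claim.

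**The error is conservative.** On the article's own numbers this is correct and should be conceded. A reader might infer that the trial is underpowered, because 2.5 looks small beside the statement that "The PCS and MCS have a maximum score of 100". A scale maximum does not fix the spread between people, and the article gives no other SD. Underpowering is a possibility that depends on assumed SDs; it is not shown.

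**The missing source for the SD and the missing loss allowance.** A reader might count these as errors too. A condensed article may leave both to the full protocol. Loss also changes little on the stated inputs: power stays above 80% until about 71% are lost.

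**A null result would be misread.** A reader might infer that the trial would claim to exclude a 2-point effect on the strength of the 80%. Nothing in the article says that a null result will be read in that way.

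**The correction changes nothing in the trial's conduct.** True: sample size, endpoint and analysis stay as they are. That makes the correction cheap; it does not make the sentence right.

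**Conclusion.** The sentence is wrong as written. Its inputs give 99.96% power, not 80%, and 80% would need 26 per arm against the planned 90. This rests on a two-sided two-sample t-test with equal arms; one-sided testing, a single province, or a pooled change score with uncorrelated visits all leave power above 96%.

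At least one of the SD, the difference, the power or the sample size is misstated, or an adjustment was used and not disclosed. The article does not show which, so the direction of the practical consequence is open: a trial far larger than its target needs if the SD of 2.5 holds, or power below 80% if the true SD is above about 4.76. The second case is conditional on SDs that the article does not supply.

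**What to change.** Keep 180 carers and restate the calculation so that sample size, difference, SD and power agree.

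- If the SD of 2.5 is correct, report about 99.96% power for 2 points, with a detectable difference of about 1.05 points at 80% power.
- If another input was misstated or an adjustment was applied, correct or disclose it and report the power that results. Do not choose an SD such as 4.76 merely because it restores 80%; the article does not establish that the SD is the wrong entry.
- State whether alpha is two-sided, and whether the SD is that of the score, the change or the baseline-adjusted score.
- Give the detectable difference with 90 per arm over a range of SDs, labelled as assumptions, as in the last table of the working.

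Cost: one paragraph of wording and no extra participants. The stated figure may become less favourable if the SD proves larger than 2.5.

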### Data collection

Trained, site-specific research assistants (data collectors) will collect all study data during pre-arranged, telephone interviews with consenting study participants at four time points: baseline, 1 month, 3 months and 6 months. All interviews will be digitally recorded and will range from 30 to 60 min in length depending on the participant’s group allocation and the data time point. Table 2 outlines the schedule of data collection by group. Data collectors will reconfirm the participant’s eligibility and obtain their verbal consent to participate prior to each telephone interview.

**Table 2 Tab2:** Schedule of data collection (Intervention and control groups)

	Initial (Baseline)	1 month (day 28)	3 months	6 months
Quantitative Data:				
Demographics	X			
Health-Related Quality of Life (SF-12v2)	X	X	X	X
Self-Efficacy (GSES)	X	X	X	X
Hope (HHI)	X	X	X	X
Use of Services (HSSUI)	X		X	X
Toolkit Checklist		I	I	
Qualitative Data		I	X	X

X = intervention and control groups; I = intervention group only

During each interview, research assistants will record participants’ responses to the survey questions electronically using e-fillable surveys accessible through ReDCap. The surveys are only marked with the participant’s unique study ID, and accessed on an encrypted study laptop dedicated to the study. Digital recordings of all semi-structured interviews will be labeled with each participant’s study ID and the respective data time point, and then uploaded to the secure SharePoint site. Interview data will be anonymized at the time of transcription, in preparation for analysis.

At the first telephone contact all participants will be sent, electronically, a study brochure with the research coordinator’s contact information, and a copy of all study questionnaires for reference only. At the time of data collection, the interviewer/data collector will obtain the participant’s verbal consent and remind them that they may follow along with the interview using the questionnaires sent previously. Research assistants will track the dates and times of all contact with participants, including email communication.

To promote participant retention, data collectors will send standardized reminder messages, by email, to participants 2 weeks prior to each scheduled interview. In the event that the participant requests a change in the date and time of an interview, or misses a scheduled interview, every effort will be made to re-schedule the interview within a reasonable amount of time, i.e., within 1 week for the 1-month interview, and within 3 weeks for the 3- and 6-month interviews.

### Data analysis

All data will be cleaned and reviewed for potential outliers. Where indicated, data collection forms and interview transcripts will be reviewed to confirm or correct any data queries. The following is the proposed analysis plan for each research question.

#### Question 1: primary outcome analysis

Intent to treat analysis using generalized estimating equations (GEE) was selected as the analytical model. Analyses will be implemented using PROC GENMOD in SAS Version 9.3 [31]. The GEE model will include the following variables: group (intervention, control), time, group x time interaction, and selected covariates (if a significant intervention effect is detected in a model without covariates). If included in the GEE, covariates will include age, gender and other variables where significant group differences are seen in a comparison at baseline. The outcome of interest is a continuous variable SF12v2 MCS. The variable of primary interest is the group and time interaction, which indicates a treatment effect if statistically significant [32]. Time will be modelled based on assessment of a plot of the mean MCS values for both groups at each time period, with time treated continuously if a linear trend is observed and categorically if a non-linear trend is observed.

GEE does not require a normal distribution and SAS offers a number of distributional choices and associated link functions. The distribution (and link) selected will be the one that best matches the distribution of MCS scores for study participants. MCS is negatively skewed in many populations, with few suitable functional distributions for this pattern. If the distribution of MCS scores is significantly negatively skewed, a reflected transformation will be applied to the MCS scores in an effort to normalize them [33] and then the normal distribution and identity link will be applied to the transformed data in the GEE.

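### The unadjusted result decides whether an adjusted model is fitted, baseline significance tests choose most of its covariates, and baseline MCS serves only as the time-0 response

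*Protocol article*

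**What the plan says.** The protocol article, under Question 1: primary outcome analysis, sets the model: "The GEE model will include the following variables: group (intervention, control), time, group x time interaction, and selected covariates". The last item carries a condition, because the model takes "selected covariates (if a significant intervention effect is detected in a model without covariates". If the condition is met, "covariates will include age, gender and other variables where significant group differences are seen in a comparison at baseline".

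The effect is read from one term: "The variable of primary interest is the group and time interaction, which indicates a treatment effect if statistically significant".

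Under Data collection, MCS is obtained in "telephone interviews with consenting study participants at four time points: baseline, 1 month, 3 months and 6 months", and Table 2 marks the SF-12v2 at all four. Baseline MCS is not named as a covariate. With time in the model, the natural reading is that it is the first of four repeated responses.

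The section on missing data has values multiply imputed before the GEE is fitted. The Secondary analysis section applies the same approach to PCS, HHI and GSES, so the rule reaches every health outcome.

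**The concern.** Three features of this rule are poorly chosen.

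- **The gate.** An adjusted estimate is produced only after the unadjusted test has succeeded. The data decide which analyses exist, and the article does not say which result counts once both do.
- **The screen.** Under 1:1 randomisation, a significant baseline difference is a chance event. Screening on it selects imbalance rather than prognostic value, and the covariate set cannot be known in advance.
- **The use of baseline MCS.** As a response at time 0, with a free group effect, it makes group x time a comparison of changes from baseline. That is valid, but less precise than adjusting for the baseline value, which is already collected.

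At stake are a primary analysis that is not fully fixed in advance and some precision that could be had without more participants or visits.

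**Working it through.** **Inputs from the article.** 1:1 allocation; 180 carers, so 90 per arm; difference 2, SD 2.5, alpha 0.05 and power 80% (Power and sample size). The sidedness of alpha is not stated; two-sided is assumed. The article gives no correlation r between baseline and follow-up MCS, so r = 0.5 to 0.7 is assumed, with equal SDs at both times.

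**The plan's own figure.** n per arm = 2(1.960 + 0.842)² x 2.5² / 2² = 24.5, so 25 per arm, or 50 in total. With 90 per arm, power is 99.97%. The stated 180 at 80% is not reproduced. That is a separate matter, but it shows that at the stated SD there is almost no power left to gain.

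**The screen.** The Caregiver demographic form lists 11 carer items besides age and gender, and 3 items on the person cared for, which makes 14 candidates. Assuming independent tests at 5% (the article gives no level for the screen):

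- 14 candidates: 1 − 0.95^14 = 51%
- 11 candidates: 43%
- 18 candidates: 60%

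**Baseline as response or as covariate.** For one follow-up visit, the per-person variance is 2(1 − r)σ² for change and (1 − r²)σ² with baseline as a covariate. The ratio is (1 − r²) / [2(1 − r)] = (1 + r)/2.

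| r | Ratio | Variance saved | Equivalent extra participants (1/ratio − 1) |
|---|---|---|---|
| 0.5 | 0.75 | 25% | 33% |
| 0.6 | 0.80 | 20% | 25% |
| 0.7 | 0.85 | 15% | 18% |

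**Power**, 90 per arm, difference 2, as Φ(2/SE − 1.96) with SE = √(2 x variance / 90):

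| SD | r | Change | Baseline-adjusted |
|---|---|---|---|
| 2.5 (stated) | 0.5 | 99.97% | above 99.99% |
| 5 (assumed) | 0.5 | 76.5% | 87.3% |
| 5 (assumed) | 0.6 | 85.1% | 91.8% |
| 5 (assumed) | 0.7 | 93.4% | 96.4% |
| 10 (assumed) | 0.5 | 26.8% | 34.1% |
| 10 (assumed) | 0.7 | 41.0% | 46.8% |

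For SD 5 and r = 0.6: SE = √(2 x 20 / 90) = 0.667 for change and √(2 x 16 / 90) = 0.596 adjusted. A simulation of 20,000 trials gives 84.6% and 91.5%.

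**Do the gated covariates move the tested term?** A covariate that is constant over time shifts all of a person's visits equally, so it cancels from a difference between visits. In a simulated complete data set (180 carers, 4 visits, identity link), the three group x time coefficients were 3.354, 1.180 and 3.602. Adding age and sex, or age, sex and province, left the coefficients and their standard errors unchanged to the printed decimals. With 20% of follow-up values missing and not imputed, the coefficients moved by at most about 0.025 (exchangeable working correlation) or 0.18 (independence).

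**The case against.** The strongest reply is that the gate and the screen do little numerical harm. The tested term is group x time, the data are imputed to completeness, and main effects of time-constant covariates cancel from that term. In 100 simulated complete data sets with strongly prognostic covariates, the significance verdict never changed. This stands, given an identity link and covariates not crossed with time. The article leaves the distribution and link open, so the cancellation is likely but not guaranteed.

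It also disposes of several stronger readings that a reader might infer:

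- **Omitting province loses precision.** Recruitment is planned as "90 in Ontario, and 90 in Alberta", but province cancels like any other time-constant term, and the article does not say that randomisation was stratified by it.
- **The adjusted and unadjusted primary estimates may conflict.** Under the conditions above they essentially coincide.
- **The gate discards significant results.** In the simulation at SD 5 and r = 0.6, only the baseline-adjusted test is significant in about 8% of trials. That compares a change score with adjustment for baseline MCS. The plan's gated model adds age, gender and imbalanced variables, so the 8% does not measure the gate.
- **Baseline MCS is ignored, or every covariate is test-selected.** Baseline MCS is in the model as an outcome, and age and gender are prespecified.
- **The type I error is inflated.** No inflation has been shown.

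An unseen analysis plan might say which model counts. It would still have to depart from the gate and the screen, which the article states outright.

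**Conclusion.** The concern holds as a weakness in how the model is specified. The significance condition and the baseline screen are explicit and should go, because they let observed results shape the analysis without any benefit. The 51% is the chance that an unplanned covariate enters; it does not measure bias in the tested term.

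The efficiency point is a valid change-from-baseline contrast set against a more precise one. The saving of 15% to 25% in variance applies to a single follow-up contrast and rests on assumed r of 0.5 to 0.7 and equal SDs. Whether it matters for power depends on the SD: not at the stated 2.5, by about 3 to 11 percentage points at an assumed 5, and by about 6 to 7 at an assumed 10.

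**What to change.** Delete the condition on a significant unadjusted effect, and delete the baseline significance screen. Prespecify one primary GEE, fitted whatever the unadjusted result: MCS at 1, 3 and 6 months on group, categorical time, group x time, baseline MCS, baseline MCS x time, age and gender. Province is optional.

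The treatment test must be redefined at the same time, as the adjusted between-group differences at 3 and 6 months. This can be a joint test, or one contrast named in advance as primary. Once baseline is a covariate, group x time tests only whether the effect varies over follow-up. With a constant true effect of 2 (SD 5, r = 0.6) that term rejected in 5.5% of 4,000 simulated trials, so leaving the test wording as it is would remove the power of the primary analysis.

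Keep the unadjusted change-from-baseline model as a sensitivity analysis. Use the same form, with its own baseline value, for PCS, HHI and GSES.

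Cost: the primary test must be reworded and the model gains a few terms. No new data are needed. The change should be made before outcome data by group are seen.

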### Study purpose

The purpose of the study is to evaluate the effectiveness of MT4C compared to an educational control group with respect to increasing hope, general self-efficacy and HRQoL and supporting participants through their experience of transitions over time. We expect to find that family carers who are allocated to MT4C intervention group will show greater improvement in hope, self-efficacy and HRQOL, at no additional cost from a societal perspective, compared to an educational control group. MT4C will be used for 3 months and we will be looking to see if the effects continue on after use for 6 months. The study will specifically address the following research questions:Does use of MT4C result in a 3 month (immediately post intervention) and 6-month (3 months after intervention) increase in HRQoL, self-efficacy, and hope, in carers of persons with ADRD and MCC compared to an educational control group?Does use of MyT4C help carers of community-dwelling older adults with ADRD and MCC deal with significant changes they experience as carers? andAre the effects/benefits of the MT4C intervention achieved at no additional cost compared to an educational control group?

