## Methods/Design

### Study design and participants

This is a multi-site, pragmatic, mixed methods, longitudinal, repeated measures, randomized controlled trial with randomized allocation to an intervention or educational control group. Recruitment and data collection began in June 2015 and is projected to be completed by June 2017. Participant data will be collected at intake (baseline) and at 1 month, 3 months, and 6 months from the beginning of the intervention. Cost data will be collected at baseline, then at 3 months and 6 months, as the cost measurement instrument asks participants to reflect upon the previous 3 months. Qualitative and quantitative data will be collected concurrently at select time points. The qualitative data will inform the quantitative data and will be integrated in the findings phase of the study. The study features two sites, one in Alberta and the other in Ontario. The CONSORT (Consolidated Standards of Reporting Trials) statement for non-pharmacological and pragmatic interventions was used to design the study and will be used to report study findings (Fig. 1). This study received ethical approval from the University of Alberta Health Research Ethics Board (# Pro00048721) and the Hamilton Integrated Research Ethics Board (#15–309).

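### With categorical time, the deciding test is a 3-df group-by-time interaction that counts month 1, although Question 1 asks only about months 3 and 6

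*Protocol article*

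**What the plan says.** The section Question 1: primary outcome analysis specifies a GEE with group, time and their interaction, and gives the reading rule: "The variable of primary interest is the group and time interaction, which indicates a treatment effect if statistically significant". The outcome is MCS: "The outcome of interest is a continuous variable SF12v2 MCS". The coding of time depends on a plot of the group means, "with time treated continuously if a linear trend is observed and categorically if a non-linear trend is observed".

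The section Study design and participants sets four assessments: "Participant data will be collected at intake (baseline) and at 1 month, 3 months, and 6 months from the beginning of the intervention". Table 2 (Data collection) confirms that the SF-12v2 is collected at all four: "Health-Related Quality of Life (SF-12v2) X X X X".

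The question that this analysis serves, under Study purpose, is narrower: "Does use of MT4C result in a 3 month (immediately post intervention) and 6-month (3 months after intervention) increase in HRQoL". It names two visits and a direction, and month 1 is not among the visits. The same section states the expected direction, namely that the MT4C group "will show greater improvement in hope, self-efficacy and HRQOL, at no additional cost from a societal perspective, compared to an educational control group".

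Nothing in the article links the interaction test to the month-3 and month-6 differences. The section Secondary analysis carries the same analysis over to PCS, hope and self-efficacy.

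**The concern.** With two groups and four categorical visits, the group-by-time interaction asks whether the change from baseline differs between groups at any of months 1, 3 or 6. That is a broader hypothesis than Question 1. A difference that appears after one month and is gone by month 3 makes the interaction true, and under the stated rule it is read as a treatment effect, although the answer to Question 1 would be no at both visits.

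At stake is the meaning of the primary result. A significant interaction would not tell the reader whether MCS was higher at the end of MT4C access or three months later. The branch is a realistic one: an effect that appears during the three months of access and then levels off or fades is not linear over 0, 1, 3 and 6 months.

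**Working it through.** **Inputs from the article.** 180 carers allocated 1:1, so 90 per arm; visits at 0, 1, 3 and 6 months; alpha 0.05 (sidedness not stated); planning difference 2 with SD 2.5, which is 2/2.5 = 0.8 SD, with no visit named.

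**Assumptions not in the article.** Compound symmetry with within-person correlation ρ = 0.5 (range 0.3 to 0.7), equal variances, no dropout, two-sided 0.05.

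**The plan's own power figure.** A two-sided comparison of two means with 90 per arm, difference 2 and SD 2.5 has power 0.9997, so the stated 80% is not reproduced. That is a separate matter, and nothing below uses the 80%.

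**Degrees of freedom.** (2 − 1) × (4 − 1) = 3.

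**Formulas.** Let d₁, d₃, d₆ be the true between-group differences in change from baseline, in SD units.
- Their estimates have covariance (2/n)(1 − ρ)(I + J), where n is the number per arm, I the identity matrix and J the matrix of ones.
- The 3-df Wald test has noncentrality λ = n/[2(1 − ρ)] × [Σd² − (Σd)²/4].
- The SE of a single-visit contrast is √[4(1 − ρ)/n]. At ρ = 0.5 this is √(2/90) = 0.149.
- The SE of the average of months 3 and 6 is √[3(1 − ρ)/n]. At ρ = 0.5 this is √(1.5/90) = 0.129.

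**Effect of 0.4 SD at month 1 only.** At ρ = 0.5, λ = 90 × (0.16 − 0.04) = 10.8.

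| ρ | λ | Interaction significant | Of these, neither month-3 nor month-6 contrast significant (simulated) |
|---|---|---|---|
| 0.3 | 7.71 | 64% | 87% |
| 0.5 | 10.8 | 80% | 89% |
| 0.7 | 18.0 | 96% | 91% |

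In the same trials a pre-named contrast at month 3, at month 6 or on their average is significant in favour of MT4C only 2.5% of the time. With the article's own planning effect (0.8 SD) at month 1 only, the interaction is significant in at least 99.9% of trials, and about 91% of those show nothing significant at month 3 or month 6.

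**Power of the alternatives, ρ = 0.5.**

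| Profile at months 1/3/6 (SD) | Interaction | Month-3 contrast | Average of months 3 and 6 |
|---|---|---|---|
| Peaked 0.2/0.4/0.2 | 60% | 77% | 64% |
| Sustained 0.4/0.4/0.4 | 80% | 77% | 87% |
| Building 0.1/0.24/0.4 | 66% | 36% | 70% |

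Example, building profile: λ = 90 × (0.2276 − 0.74²/4) = 90 × 0.0907 = 8.16, which gives 66%. Month 3: 0.24/0.149 = 1.61 and Φ(1.61 − 1.96) = 36%. Average: 0.32/0.129 = 2.48 and Φ(2.48 − 1.96) = 70%.

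**The case against.** **Follow-up contrasts belong to the analysis plan.** A plan that is not shown may well name contrasts, and their absence from an article would be no finding. But the article does more than stay silent: it fixes the interaction as the quantity of primary interest and says how significance is to be read. The mismatch with Question 1 lies in that rule.

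**The month-1-only profile is chosen for effect.** MT4C access runs for the full three months, and nothing in the article predicts an effect that vanishes by month 3. A month-1 difference is also a real effect, and the interaction test holds its 5% level. All of this stands. The percentages show what the rule permits; they do not say how likely the profile is.

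**The interaction is not a weak test.** This also stands. No option wins under every profile, and at effects near 0.8 SD the power differences all but vanish. The point therefore rests on the mismatch and not on lost power.

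**Stronger readings that the article does not support.**
- A reader might infer that worsening under MT4C could be declared a success, because a 3-df test has no sign. The article says only that significance indicates a treatment effect, it states the expected direction, and the fitted estimates would show the sign.
- A reader might infer an inflated error rate from claiming on either the 3- or the 6-month contrast (9.1% under the assumptions above). That needs an analyst who departs from the stated rule.
- A reader might say that the plan does not settle which test decides. It does: the interaction decides.

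**Conclusion.** The concern holds in limited form. If time is categorical, the deciding test spans months 1, 3 and 6, while Question 1 concerns months 3 and 6, so a month-1-only difference meets the rule. How often this would happen depends on an effect profile and a correlation that the article does not give; the 80% (64% to 96%) and 89% (87% to 91%) figures hold for the assumed 0.4 SD month-1 effect. The 3-df structure and the mismatch follow from the text alone.

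The point does not cover the branch with continuous time, where the interaction is a 1-df slope difference. It should be corrected because the remedy is cheap, but it does not make the trial's data unable to answer Question 1.

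**What to change.** In Question 1: primary outcome analysis, replace the overall interaction as the deciding test with one pre-named, signed, 1-df contrast of the between-group difference in MCS change from baseline. Either of these answers Question 1:
- the average of the month-3 and month-6 differences; or
- the month-3 difference, followed by month 6 only if month 3 is significant.

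Test at two-sided 0.05, conclude benefit only if the contrast favours MT4C, and report month 1 and the overall interaction descriptively. State the sign convention as well, because the section allows a reflected transformation of MCS, which reverses the direction. Secondary outcomes that borrow this analysis should take the same contrast.

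**Cost.** About two sentences and no new data; the categorical GEE fit already supplies the contrasts. A month-1-only difference could no longer carry the primary claim. The month-3-first version loses power if the effect builds to month 6 (36% against 66% for the interaction in the building profile), and it gives month 3 priority where Question 1 gives none. The average did better than the interaction in all three profiles tried (64% vs 60%, 87% vs 80%, 70% vs 66%), but it does not by itself show an effect at each visit, so both visit-specific estimates should be reported beside it.
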